## Abstract

**Background:**

Chronic orofacial pain (COP) is common, costly, and associated with substantial pain interference and emotional distress. Psychosocial treatments for COP are scarce and limited (eg, rely on talking, which is often painful for this population; require intensive resources, limiting scalability). Here, we describe the study protocol for developing *Face-Forward-Web*, a “talk-free” web-based mind-body intervention for patients with COP.

**Objective:**

We aim to (1) develop *Face-Forward-Web* with the aid of live-video focus groups with adults with COP and (2) optimize *Face-Forward-Web* and our study protocol through beta testing followed by an open feasibility trial.

**Methods:**

We will accomplish these aims in 2 phases, incorporating user-centered design principles. For phase 1, we conducted semistructured focus groups (n=4 groups, 22 participants) with individuals with COP. We are using rapid data analysis followed by thematic analysis to gauge treatment needs, preferences, and perceptions of the proposed platform and skills. This information will inform session structure and content as well as development of a wireframe followed by a prototype. For phase 2, we will conduct beta testing (up to n=10) followed by a feasibility trial (up to n=20) with exit interviews to gather feedback. The primary outcomes are feasibility benchmarks such as recruitment (≥70% of the eligible participants will participate), acceptability (≥70% of the participants complete ≥4 or 5 sessions), credibility, expectancy (≥70% above the Credibility and Expectancy scale’s midpoint), and satisfaction (≥70% above the User Experience Questionnaire’s midpoint).

**Results:**

Recruitment for phase 1 began in October 2024 and concluded in January 2025. Data analysis for phase 1 will conclude in fall 2025 and for phase 2 in 2026. Results will iteratively guide the development of the intervention.

**Conclusions:**

*Face*-*Forward-Web* will be the first talk-free web-based intervention tailored to the needs of adults with COP. Results will inform a future efficacy trial.

**Trial Registration:**

ClinicalTrials.gov NCT06754917; https://clinicaltrials.gov/study/NCT06754917

**International Registered Report Identifier (IRRID):**

DERR1-10.2196/71839

## Introduction

Chronic orofacial pain (COP) is common [1], costly [2], and associated with substantial pain interference (ie, pain-related activity limitations) and emotional distress [3-5]. COP includes a group of conditions that involve pain in the hard and soft tissues of the head, face, and neck that last for more than 3 months [6]. Although the etiological aspects of COP are heterogeneous, COP conditions are unified by a psychosocial profile of substantial maladaptive coping (eg, pain-related fear, pain catastrophizing) [7-9], pain interference, and emotional distress (eg, depression, anxiety) [3,4,10-14], which worsen each other over time [15,16]. Treatments are typically biomedical [4], mostly ineffective [17], and often involve adverse side effects [18], misdiagnoses or incomplete diagnoses [17], and unnecessary/painful procedures (eg, tooth extractions, occlusal adjustment) that may lead to irreversible damage [4,19]. Such treatments do not typically address and often exacerbate activity limitations, maladaptive coping, and emotional distress [4,19]. These psychosocial factors are critical causative elements of COP but are mostly overlooked in COP treatment [20].

Psychosocial interventions such as cognitive behavioral therapy [21-28] and other behavioral programs [29-32] show promise in improving outcomes in individuals with COP [21-32]. However, the existing interventions are limited in several ways: these interventions (1) almost exclusively rely on talking, which is often painful for patients with COP and limits treatment engagement [20,33]; (2) are resource-intensive and require availability of trained providers, limiting accessibility, particularly for underserved communities [34]; (3) often involve costs, travel, and limited insurance coverage [35]; (4) carry a mental health stigma, which limits treatment-seeking and participation [36]; (5) tend to focus on an incomplete diagnosis and mostly temporomandibular disorder, limiting generalizability, and (6) are typically unimodal (eg, cognitive behavioral therapy alone), despite evidence that multimodal interventions work better for complex conditions like COP, which have high psychiatric comorbidity [24,37]. Talk-free asynchronous multimodal web-based platforms can bypass these limitations while maintaining effectiveness [38]. However, to our knowledge, no such interventions exist. Delivering COP interventions through a web-based platform holds potential to expand accessibility, increase scalability, and address this population’s largely unmet needs [20,39].

To this end, we will develop *Face-Forward-Web,* the first web-based platform adapted and refined via mixed methods for COP by using user-centered design principles [40-43]. *Face-Forward-Web* will be adapted from *GetActive*, a mind-body and activity intervention for individuals with chronic musculoskeletal pain [44]. *Face-Forward-Web* will be delivered via a talk-free asynchronous web platform and will address some of the unique and often unaddressed challenges faced by individuals with COP, including difficulty with talking due to pain [20,33], emotional distress [3,5,20], orofacial pain interference and pain intensity [8], and coping with unpredictable pain [20].

Our conceptual model (Figure 1) is informed by the fear-avoidance framework [45,46] and poses that improvement in pain interference, pain, and emotional distress after participation in *Face-Forward-Web* will be explained by improvement in the mechanistic targets of pain catastrophizing, fear of pain, and mindfulness. Our guiding hypothesis (to be tested in future work) is that the *Face-Forward-Web* intervention will be an effective, efficient, and scalable strategy to address the unmet needs and challenges of pain interference and distress among patients with COP.

**Figure 1 figure1:**
[figure not shown]
The Face-Forward-Web conceptual model.

This study aims to (1) develop *Face-Forward-Web* with the aid of live video focus groups with adults with COP and (2) optimize *Face-Forward-Web* and our study protocol through beta testing (n=up to 10) to refine the intervention followed by a feasibility trial (n=up to 20). The results will inform future efficacy research, evaluating *Face-Forward-Web* versus an active control web platform in improving pain interference, depression, and anxiety.

## Methods

### Study Design and Setting

This study protocol adheres to the SPIRIT (Standard Protocol Items: Recommendations for Interventional Trials) 2013 statement (Multimedia Appendix 1). Our approach is consistent with the National Institutes of Health (NIH) stage model for behavioral intervention development [47,48]. The proposed phases address stages 1A (intervention development and refinement) and 1B (feasibility testing). For phase 2, the primary outcomes are feasibility benchmarks (ie, feasibility of recruitment, credibility and expectancy, acceptability of treatment, adherence to homework, satisfaction [user experience], feasibility of assessments, adverse events).

This study will be completed in 2 main phases conducted at a large academic hospital. In phase 1, we conducted 4 virtual focus groups (22 patients with COP) at which point we reached saturation [49]. We aimed to understand their treatment needs and preferences, perceptions, and recommendations for a web platform delivery, and the best ways to engage and retain participants. We also gathered participants’ feedback on program content via sample videos similar to those intended to be used in the *Face-Forward-Web* program. We are using this information to inform adaptations from the *GetActive* intervention for chronic musculoskeletal pain intervention to the *Face-Forward-Web* intervention for chronic orofacial pain as well as for the development of a wireframe for *Face-Forward-Web*, followed by a prototype [42].

In phase 2, we will conduct beta testing (up to n=10) and revise *Face-Forward-Web* and the study procedures according to the feedback and information gathered. We will then conduct a feasibility trial (up to n=20) with rapid iterative development of the prototype intervention [50].

### Inclusion and Exclusion Criteria

We plan to include participants aged ≥18 years, with English fluency and literacy, chronic nonmalignant COP (>3 months), who express ability and willingness to participate in a live-video focus group/web platform intervention, are free of concurrent psychotropic medications for at least 2 weeks prior to treatment, or stable on current psychotropic medication for ≥6 weeks, and have pain intensity ≥4/10. We will exclude individuals who practiced mindfulness >45 min/wk in the past 3 months and those who have participated in mind-body or cognitive behavioral therapy in the past 3 months; have severe untreated mental health (eg, psychosis) or active suicidal ideation; or are pregnant (per our institutional review board).

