### Procedures

#### Ethical Considerations

Methodology, including interview script and recruitment strategies and materials, were approved by the institutional review board of the Massachusetts General Hospital. The institutional review board determined that phase 1 activities were exempt from written informed consent. Instead, all participants viewed an online study fact sheet during enrollment and provided consent to participate (protocol 2024P001309). Participants in phase 2 will provide written informed consent and may opt out at any time during the study (protocol 2024P003501). All focus group and exit interview transcripts are deidentified prior to analysis, and any quantitative data exported for analysis will also be deidentified. Participants can receive payment up to US $50 via check for completing all phase 1 activities and up to US $170 for completing all phase 2 activities.

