#### Phase 2: Beta Testing and Feasibility Trial With Exit Interviews

##### Beta Testing

After screening, consent, and enrollment, up to 10 individuals with COP will beta test *the Face-Forward-Web* intervention. The research coordinator will schedule an orientation session, in which she will outline how to navigate the *Face-Forward-Web* platform. Participants will then independently complete the intervention. After each module, participants will be asked to indicate their level of satisfaction from the module on a 1-4 Likert scale and provide feedback on their impressions from the module in a textbox. At the conclusion of the intervention, participants will participate in exit interviews over Zoom. Exit interviews will last ~30 minutes and will be audio-recorded and transcribed. Similar to phase 1, the exit interviews will involve a semistructured script, followed by rapid data analysis and qualitative thematic analysis using NVivo 12. We will utilize results to further refine the intervention’s content manual and procedures as well as refine *Face-Forward-Web* prior to the feasibility trial.

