##### Feasibility Testing

Participants will be recruited, screened, and enrolled using the methods described above. After consenting, participants (n=up to 20) will complete a set of valid and reliable online questionnaires over the secure Research Electronic Data Capture (REDCap) system. The estimated time for completion is 20 minutes. If participants miss an item, they will be prompted to complete it, thereby minimizing missing data. Participants will complete the questionaries at 2 additional timepoints—after completing the intervention and again 3 months later. After baseline assessments, participants will participate in an orientation session. Then they will complete the intervention and subsequent exit interviews following similar procedures as in the beta testing.

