#### Phase 2: Beta and Feasibility Testing With Exit Interviews

We will use frequency and proportions to assess the feasibility of the recruitment and retention procedures. We will determine treatment satisfaction and credibility by the proportion of participants who score above the scale midpoint in the User Experience Questionnaire [65] and Credibility and Expectancy Questionnaire [66], respectively. See Table 2 for further details on the feasibility, credibility, and acceptability benchmarks, consistent with other established feasibility work [67-69]. We will analyze qualitative data from the exit interviews by using the same procedures described in phase 1.

**Table 2 table2:** Feasibility benchmarks.

Outcome	Acceptable	Excellent
Credibility and expectancy	>70% of the participants with score over scale midpoint.	>75% of the participants with score over scale midpoint.
User experience	>70% of the participants with score over scale midpoint.	>75% of the participants with score over scale midpoint.
Feasibility of recruitment	>70% of eligible participants agree to participate.	At least 80% of eligible participants agree to participate.
Acceptability of treatment	>70% of the participants attend 3 out of 5 sessions.	>80% of the participants attend 3 out of 5 sessions.
Adherence to homework	>70% of the participants practice >1 skill on 3 d/wk.	>80% of participants practice >1 skill on 3 d/wk.
Feasibility of assessments	>70% of the participants have no measures fully missing.	>90% of the participants have no measures fully missing.
Adverse events	Minimal	None

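### The recruitment benchmark is partly circular and biased upward, because people unwilling at screening are ineligible and so leave its denominator

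*Protocol article*

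**What the plan says.** Under Inclusion and Exclusion Criteria, the protocol article lists among the conditions for entry that participants be people "who express ability and willingness to participate in a live-video focus group/web platform intervention". One set of criteria serves both phases. For phase 2 the relevant half of that phrase is the web platform intervention, which is the treatment being tested.

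Table 2 (Data Analysis, Phase 2) rates recruitment as acceptable if ">70% of eligible participants agree to participate" and as excellent if the following holds: "At least 80% of eligible participants agree to participate". The Abstract uses the same denominator: "recruitment (≥70% of the eligible participants will participate". Study Design and Setting gives the benchmark its status: "the primary outcomes are feasibility benchmarks (ie, feasibility of recruitment, credibility and expectancy, acceptability of treatment".

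On the order of steps, Beta Testing says "After screening, consent, and enrollment, up to 10 individuals with COP will beta test", and Feasibility Testing carries the procedure over: "Participants will be recruited, screened, and enrolled using the methods described above". Ethical Considerations adds a separate consent step: "Participants in phase 2 will provide written informed consent and may opt out at any time during the study".

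The article does not set the willingness criterion aside when the denominator is counted. Nor does it say at what moment a person is fixed as eligible.

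**The concern.** A recruitment rate is meant to show what share of suitable people take up the study when it is offered. Here part of the answer is built into the definition of suitable. A person who meets every clinical criterion but does not want the web platform fails an inclusion criterion. Followed as written, that person leaves the denominator, although this is the refusal the benchmark exists to detect.

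The error runs one way. Removing decliners from the denominator can raise the rate but never lower it. The benchmark is one of the phase 2 primary outcomes, and the article says the results will inform a later efficacy trial against an active control platform. A recruitment result that reads acceptable or excellent when uptake is lower would give false reassurance at that point. The problem arises from two rules that the article states, not from detail left out of a condensed text.

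**Working it through.** The plan states no expected uptake, refusal rate or error rate for this benchmark, so there is no figure of its own to reproduce. The check shows how the measured rate depends on where decliners are recorded.

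**Inputs from the article**
- Enrolled, E = 20, the maximum for the feasibility trial (Feasibility Testing).
- Thresholds: above 70% for acceptable and at least 80% for excellent (Table 2).

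**Assumed inputs (not in the article)**
- True uptake u: the share of people meeting all other criteria who join. It is varied from 30% to 60%.
- Screen-out share s: the proportion of decliners classed as ineligible through the willingness criterion. It is varied from 0 to 1.

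**Formulas**
- Decliners: D = E/u − E.
- Measured rate: R = E / (E + D × (1 − s)).

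**Room before the benchmark fails.** With 20 enrolled, 8 counted decliners give 20/28 = 71.4% (pass) and 9 give 20/29 = 69.0% (fail). For the excellent level, 5 decliners give 20/25 = 80%. The Abstract has at least 70% where Table 2 has above 70%. This makes no difference with 20 enrolled, because 20/0.70 = 28.57 is not a whole number of people.

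**Worked case, u = 50%.** D = 20/0.5 − 20 = 20.
- s = 0: 20/40 = 50%
- s = 0.25: 20/35 = 57%
- s = 0.50: 20/30 = 67%
- s = 0.75: 20/25 = 80%
- s = 1: 20/20 = 100%

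**Other assumed uptakes**

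| True uptake | Decliners D | s = 0.25 | s = 0.50 | s = 0.75 | s = 1 | s above which R exceeds 70% |
|---|---|---|---|---|---|---|
| 30% | 46.7 | 36% | 46% | 63% | 100% | 82% |
| 40% | 30.0 | 47% | 57% | 73% | 100% | 71% |
| 50% | 20.0 | 57% | 67% | 80% | 100% | 57% |
| 60% | 13.3 | 67% | 75% | 86% | 100% | 36% |

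The last column is 1 − (20/0.70 − 20)/D. For u = 50% this is 1 − 8.57/20 = 57%. R depends only on u and s, so choosing E = 20 does not drive the percentages.

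**The same point from the other side.** Assume 90% of people who say they are willing go on to consent. The measured rate is then 90% however many were unwilling. If 30% of otherwise eligible people are unwilling, true uptake is 0.70 × 0.90 = 63%, below the threshold. True uptake falls below 70% once more than 1 − 0.70/0.90 = 22% are unwilling.

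**The case against.** A reader might infer that everyone who declines drops out of the denominator, that the rate must sit near 100%, and that the benchmark can hardly fail. The article does not support this. Written consent in phase 2 is a separate step listed after screening, so someone who is willing at screening and then refuses consent is an eligible decliner and is counted. In the table above, a true uptake of 50% still fails the benchmark when a quarter or half of decliners are screened out. The 100% reading is the limiting case s = 1.

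The criterion also has a narrower reading. It pairs willingness with ability and names the delivery format, so it may ask only whether a person can and would use video or web delivery. On that reading, someone who accepts the platform but declines the three rounds of questionnaires, the recorded exit interview or the activity tracking is an eligible refusal. This reading shrinks the overlap but does not remove it, because refusing the web platform is refusing the intervention under test.

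Other points on that side also stand. The article does not describe how a refusal at screening is logged, and the consent and unwillingness rates used above are assumptions. No passage says this rate will be used to project recruitment, only that the results will inform a later trial. Recruitment is partly through social media and an advocacy association, so even a repaired rate describes people who reached screening, not all patients.

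It can also be argued that refusal coding is operational detail which an article leaves to the full protocol. That does not dispose of the point, because the article itself states both the criterion and the denominator, and together they determine the bias.

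**Conclusion.** The point holds as an upward bias through partial circularity. As the two rules stand, people unwilling at screening are ineligible, and only those who change their mind or refuse at consent count against recruitment. The benchmark is tautological only if willingness and agreement are judged at the same moment, and the article does not say that they are.

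The direction of the bias is certain wherever any decliner is classed as ineligible through this criterion. Its size cannot be computed from the documents. It depends on true uptake and on the share of decliners screened out, both assumed here. Under those assumptions the effect runs from a few percentage points to turning a clear failure into the excellent category: a true uptake of 50% reads as 80% when three quarters of decliners are screened out. That is enough to justify changing the definition of a primary outcome before phase 2 screening begins.

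**What to change.** For the recruitment benchmark only:

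- Define the denominator as everyone screened who meets all inclusion and exclusion criteria other than willingness and who is offered the study.
- Count unwillingness at screening as a refusal, and record the reason.
- State the moment at which eligibility is fixed for this count.
- Report decliners at screening and decliners at consent separately, so that reluctance about the platform can be told apart from reluctance about the study's other demands.

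Willingness stays a condition of enrolment, so nobody's eligibility changes. The cost is a sentence with Table 2, the same denominator in the Abstract, and one column in the screening log. The drawback is that the reported rate may look less favourable. As of August 2025 the article describes intervention content as only being started, with phase 2 analysis due in 2026, so there is probably still time to make the change before phase 2 screening.

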### Recruitment

For both phases of the study, we will recruit from sources such as the Facial Pain Association—a large organization providing support, education, and advocacy for individuals with COP—the Facial Pain Clinic at Massachusetts General Hospital, social media, and other sources. We will prioritize recruitment of racial and ethnic minorities and aim to reflect the US population (38% of the minorities). Individuals who participate in phase 1 focus groups may participate in phase 2 feasibility testing.

### Procedures

#### Ethical Considerations

Methodology, including interview script and recruitment strategies and materials, were approved by the institutional review board of the Massachusetts General Hospital. The institutional review board determined that phase 1 activities were exempt from written informed consent. Instead, all participants viewed an online study fact sheet during enrollment and provided consent to participate (protocol 2024P001309). Participants in phase 2 will provide written informed consent and may opt out at any time during the study (protocol 2024P003501). All focus group and exit interview transcripts are deidentified prior to analysis, and any quantitative data exported for analysis will also be deidentified. Participants can receive payment up to US $50 via check for completing all phase 1 activities and up to US $170 for completing all phase 2 activities.

#### Phase 1: Developmental Phase With Focus Group Feedback

We have developed a semistructured qualitative interview script with items assessing treatment needs, preferences, and perceptions of the intervention skills and structure (Multimedia Appendix 2). We completed recruitment and data collection for phase 1 in January 2025. We recruited individuals with COP. Study staff screened potential participants and obtained verbal consent. Then, eligible patients were invited to participate in one of the 4 focus groups. Upon enrollment, participants completed an electronic demographic questionnaire and were aided with downloading and installing the video software (Zoom) as needed. All qualitative interviews were audio-recorded, transcribed, organized, and analyzed using the NVivo 12 qualitative statistical package (QSR International). We will use the qualitative results of phase 1 to develop *Face-Forward-Web* and the treatment manual to be piloted in phase 2.

